#### Participant follow-up

Clinical follow-up will take place at 3, 6, and 9 months and 1 year by clinical visit or telephone interview if needed. Laboratory follow-up will take place at 3 months (not obligatory) and 1 year. Follow up CAG and VH-IVUS will take place 12 months after randomization. At all planned contacts during the treatment period, patients will be asked whether they have adhered to the correct drug administration. Subjects with trial-related adverse events during the study period will be compensated for the standard of care by LIG Insurance Co., Ltd (Seoul, Korea).

## Statistical considerations

### Sample size calculations

Based on a previous study [15], a sample size of approximately 42 patients per treatment group was calculated to provide 80% power (assuming a standard deviation of 7.82) to detect a difference of 4.78 in percentage NCV and to detect the superiority of statin plus fenofibrate compared to statin alone with a two-sided alpha level of 0.05. With a statin plus fenofibrate:satin alone sampling ratio of 1:1 and a dropout rate of 20%, a final sample size of 53 patients per treatment group (total 106 patients) was specified in order to provide an adequate number of evaluable patients. To the best of the researchers’ knowledge, no study has been conducted on the change of tissue characteristics after fenofibrate treatment. We hypothesized that fenofibrate has an effect on percentage NCV as much as that of 10 mg atorvastatin [15]. In addition, a previous study [16] consisting of 100 patients with non-significant lesions demonstrated a significant decrease in NCV in the rosuvastatin (10 mg/day) treated group but not in the simvastatin treated group (20 mg/day).

### Statistical analyses

The primary endpoint of percentage NCV and absolute NCV will be analyzed using a paired-sample *t*-test or Wilcoxon rank-sum test for changes within each group, and an unpaired *t*-test or Mann–Whitney U test for differences between the two groups. Continuous variables will be expressed as mean ± standard deviation and compared by either a Student’s *t*-test or Mann–Whitney U test based on whether or not the data are normally distributed. Categorical variables will be expressed as number or percentage and compared by χ^2^ or Fisher’s exact test. Pearson correlation test will be used to evaluate the correlation between the changes in percentage NCV and absolute NCV, and changes in laboratory findings from baseline to follow-up. These statistical analyses will be performed in the entire index non-culprit segment and the most severe 10-mm segment centered on the minimal lumen area.

Multivariable linear regression analysis will be performed in order to identify the independent predictors of the reduction in percentage NCV. To analyze the secondary endpoints, VH-IVUS parameters, grey IVUS parameters, and angiographic parameters will be analyzed using a paired sample *t*-test or Wilcoxon rank-sum test for changes within each group, and an unpaired *t*-test or Mann–Whitney U test for differences between the two groups. Correlations between these parameters and laboratory variables will be evaluated by the Pearson correlation test.

Changes in the phenotypes of the index lesions between the two groups will be compared by χ^2^ or Fisher’s exact test. The composite endpoint of CV events will be analyzed by comparing the Kaplan–Meier event rates using a log-rank test. A *p* value < 0.05 will be considered statistically significant.

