### Research materials

#### VH-IVUS and quantitative coronary angiography

VH-IVUS using a synthetic-aperture-array, 20-MHz, 3.2-French catheter (Eagle Eye, In-Vision gold, Volcano Corp, rancho Cordova, CA, USA) with motorized catheter pullback (0.5 mm per second) after intracoronary administration of nitroglycerin 0.2 mg will be performed in non-culprit lesions with intermediate stenosis. During pullback, grayscale IVUS is recorded and raw radiofrequency data are captured at the top of the R wave for the reconstruction of the color-coded map by a VH-IVUS data recorder (Volcano Therapeutics). Enrolled lesions will be native vessels and should be located more than 10 mm apart from the intervened lesion. Cases where the patients’ condition is unstable or the characteristics of the lesions make it difficult to perform VH-IVUS in terms of severe angulated lesions, calcified lesions, or thrombus containing lesions, will be excluded.

Data from the VH-IVUS and CAG will be measured by an independent investigator who is blinded to patient group and characteristics. Data from VH-IVUS, such as percentage and absolute NCV, DC volume, F volume, FF volume, and presence of thin cap fibroatheroma (TCFA), and data for the gray IVUS, such as external elastic membrane, lumen, plaque volume, and the remodeling index, will be measured in the entire index segment and the most severe 10 mm segment centered on the minimal lumen area at baseline and after 12 months.

Data from CAG, such as reference vessel diameter, minimal lumen diameter, and lesion lengths, will be measured by a dedicated quantitative coronary angiography (QCA) program.

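### The plan names the Wilcoxon rank-sum test, an independent-samples test, for paired within-group changes; it should be the signed-rank test, and only supportive analyses are affected

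*Protocol article*

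**What the plan says.** The Statistical analyses section of the protocol article gives two tests for each of two questions about percentage and absolute NCV. For change over time inside an arm it offers a paired t-test or a "Wilcoxon rank-sum test for changes within each group". For the comparison of arms it offers an unpaired t- "test or Mann–Whitney U test for differences between the two groups".

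The following paragraph repeats the scheme for the secondary endpoints: "VH-IVUS parameters, grey IVUS parameters, and angiographic parameters will be analyzed using a paired sample" t-test, with the rank-sum test again as the non-parametric alternative within groups. The signed-rank test is named nowhere in the article.

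The data for the within-group question are paired. The section on VH-IVUS and quantitative coronary angiography has the imaging variables measured in the whole index segment and in the "most severe 10 mm segment centered on the minimal lumen area at baseline and after 12 months".

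**The concern.** The rank-based partner of the paired t-test is the Wilcoxon signed-rank test, which works on the within-lesion differences. The Wilcoxon rank-sum test pools two samples that are taken to be independent, and it is the same procedure as the Mann–Whitney U test. Each of the two sentences therefore gives one independent-samples test, under two names, to both a paired and an unpaired question. It also sets a test that uses the pairing beside one that discards it, as though they were interchangeable.

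An analyst who programs the text literally would compare the baseline values with the 12-month values as if they came from different patients. The correlation between the two readings of a lesion would be ignored, and real within-arm changes could be missed.

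**Working it through.** **1. The plan's own sample size, and whether this point touches it.** Inputs from Sample size calculations: difference 4.78, SD 7.82, power 80%, "with a two-sided alpha level of 0.05", dropout 20%.

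- n per arm = 2 × [(1.960 + 0.842) × 7.82 / 4.78]² = 42.01. The article states approximately 42. Rounding up gives 43, and normal-approximation power at 42 is 79.99%.
- 42 / (1 − 0.20) = 52.5, so 53 per arm and 106 in total, as stated.

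The figure reproduces. It is a between-arm calculation, sized "to detect a difference of 4.78 in percentage NCV", so the choice of within-group test does not enter it.

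**2. Size of the rank-sum test on paired data.** If the two occasions have the same continuous distribution (the null), the variance of the rank-sum statistic in large samples is (1 − ρs) times the value that the test assumes, where ρs is the population Spearman correlation between occasions. The true two-sided level is therefore 2Φ(−1.96 / √(1 − ρs)). For bivariate normal data ρs = (6/π) arcsin(ρ/2). The article gives no correlation, so ρ is an assumption shown over a range.

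| ρ | ρs | 1.96 / √(1 − ρs) | True level |
|---|---|---|---|
| 0 | 0 | 1.960 | 5.0% |
| 0.3 | 0.288 | 2.322 | 2.0% |
| 0.5 | 0.483 | 2.725 | 0.6% |
| 0.7 | 0.683 | 3.481 | 0.05% |

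**3. Simulation with 42 pairs.** Normal data, two-sided 0.05, true shift of 0.4 of the single-occasion SD. The shift is illustrative.

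| ρ | Rank-sum type I error | Rank-sum power | Signed-rank power |
|---|---|---|---|
| 0 | 5% | 42% | 41% |
| 0.3 | 2% | 41% | 56% |
| 0.5 | 0.8% | 40% | 70% |
| 0.7 | about 0.1% | 37% | 89% |

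Repeat runs differ from these power figures by about one percentage point. Signed-rank type I error stays near 5% throughout. The simulated levels agree with step 2.

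**4. A second scaling.** Read the stated SD of 7.82 as the SD of the change (an assumption) and take an illustrative within-arm change of 3.5. Signed-rank power is then about 79% at every ρ. Rank-sum power is 80% at ρ = 0, 67% at 0.3, 51% at 0.5, 24% at 0.7 and 0.3% at 0.9. At ρ = −0.3 the rank-sum level rises to 8.6%, but a negative correlation is not what one expects from two readings of the same lesion.

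**The case against.** The strongest reply is that this is a naming slip and no more. In both sentences the test stands beside the paired t-test, is assigned to within-group change, and is contrasted with the independent-samples pair. A competent analyst would probably run the signed-rank test. That is likely, and it lowers the severity. It does not make the text right: the wrong name appears twice, and nothing in the article corrects it.

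A second reply is that the power figures depend on chosen inputs. This stands. The correlation is assumed, and the loss disappears at zero. The simulated data are also normal, whereas the section lets the choice of test for continuous variables depend on normality, so normal data would go to the paired t-test. The power figures are therefore illustrative. The loss of nominal level is less fragile: the formula in step 2 of the working needs only equal continuous distributions on the two occasions and a positive rank correlation, not normality.

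A reader might also infer that the primary result is compromised. The documents do not support that. Study objectives and hypotheses states superiority between arms, Study endpoints defines the primary endpoint as a between-group comparison of change, the sample size is built on that comparison, and the test named for it is an unpaired one.

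Nor do they support a fear of excess false positives, since with positive correlation the error runs the other way. The worry that an effect might be claimed because one arm reaches significance and the other does not is speculation about later reporting; the article nowhere says that a within-arm p-value decides the trial.

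**Conclusion.** The point holds, within limits. The Statistical analyses section names an independent-samples test for paired data, once for percentage and absolute NCV and once for the secondary VH-IVUS, grey-scale IVUS and angiographic parameters. Taken literally, and assuming a positive baseline to follow-up correlation, the within-group tests would be conservative and would lose power: roughly 15 percentage points at correlation 0.3 (56 − 41), 30 at 0.5 (70 − 40) and 52 at 0.7 (89 − 37) in the illustrative setting, and none at 0.

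Only the supportive within-group analyses are affected. Severity is minor to moderate: wrong as written, probably a slip, with no bearing on the primary between-group comparison or on the planned 106 patients.

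**What to change.** In Statistical analyses, replace the Wilcoxon rank-sum test by the Wilcoxon signed-rank test in both sentences on within-group change, and carry the same wording into any analysis plan that repeats them. Leave the Mann–Whitney U test for the between-group comparison as it is.

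The cost is one word in each of two places. Sample size, data collection and timetable do not change. The article reports recruitment still open at 102 of 106, so the correction can be made before the analysis. Whether to report within-group changes as descriptive estimates with confidence intervals is a separate reporting preference and does not follow from the misnamed test.

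### The rank test named for within-arm change from baseline to 12 months is a test for independent samples; the paired data call for the signed-rank test

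*Protocol article*

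**What the plan says.** The Statistical analyses section of the protocol article describes two kinds of comparison for percentage and absolute necrotic core volume (NCV).

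- Within each arm: the paired t-test or "Wilcoxon rank-sum test for changes within each group".
- Between arms: "an unpaired *t*-test or Mann–Whitney U test for differences between the two groups".

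The same pair of tests is repeated for the secondary endpoints, in the sentence stating that "VH-IVUS parameters, grey IVUS parameters, and angiographic parameters will be analyzed using a paired sample" t-test or its rank alternative. For continuous variables in general, the choice between t-test and rank test is "based on whether or not the data are normally distributed".

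The section on VH-IVUS and quantitative coronary angiography shows that the within-arm data are paired. The index segment, and its most severe 10 mm part "centered on the minimal lumen area at baseline and after 12 months", are measured in the same patient on both occasions. The signed-rank test is not mentioned anywhere in the article.

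**The concern.** The Wilcoxon rank-sum test and the Mann–Whitney U test are one procedure, for two independent samples. The plan therefore assigns the same test to a paired question and to an unpaired one. The rank test that corresponds to the paired t-test is the Wilcoxon signed-rank test.

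A rank-sum test cannot be run on a single column of within-patient changes. Someone following the text would have to enter baseline values as one sample and 12-month values as the other, and the link between a patient's two scans would be lost. The resulting p-value does not have its nominal error rate.

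What is at stake is the within-arm p-values for NCV, the other plaque components, grey-scale IVUS and angiographic measures, wherever the rank test is used, for both the entire segment and the 10 mm segment.

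**Working it through.** **Step 1. The plan's own sample size, to see whether this test enters it.** Inputs from Sample size calculations: difference 4.78, SD 7.82, 80% power, "with a two-sided alpha level of 0.05", 1:1 allocation, 20% dropout.

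- n per arm = 2 × (1.96 + 0.8416)² × 7.82² / 4.78² = 42.01, against the stated 42. Strict rounding up gives 43.
- Power at 42 per arm = Φ(4.78/7.82 × √(42/2) − 1.96) = Φ(0.841) = 80.0%. The t-based value is 79.1%.
- 42 / (1 − 0.20) = 52.5, rounded up to 53 per arm, 106 in total.

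The figure reproduces from the two-arm formula. No within-arm test enters it.

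**Step 2. Size of the rank-sum test on paired data.** Let both scans have the same variance σ² and correlation r within patient, with n pairs. The mean difference has true variance 2σ²(1 − r)/n. A two-independent-samples test assumes 2σ²/n, which is too large by the factor 1/(1 − r). The approximate true type I error at a nominal 5% is 2Φ(−1.96/√(1 − r)). Simulation with 42 pairs (3,000 runs per setting, normal and right-skewed data) checks this.

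| r (assumed) | Formula | Rank-sum, normal | Rank-sum, skewed |
|---|---|---|---|
| 0.3 | 1.9% | 1.8% | 1.9% |
| 0.5 | 0.56% | 1.1% | 0.8% |
| 0.7 | 0.035% | 0% | 0.07% |

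A further run gave 2.6%, 0.3% and 0.07%, so the scatter at r = 0.5 is simulation noise around roughly half a percent. Across all correlations tried, from 0 to 0.9, the signed-rank test stayed between 4.2% and 5.9%.

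**Step 3. Power where the rank test would be used.** Since the choice depends on normality, skewed data are the relevant case. The assumed model is a log-normal volume with log-SD 0.7, a 20% fall, 42 pairs, and r on the log scale.

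| r (assumed) | Rank-sum | Signed-rank |
|---|---|---|
| 0.3 | 26% | 35% |
| 0.5 | 24% | 46% |
| 0.7 | 18% | 66% |
| 0.8 | 15% | 83% |

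Repeat runs move these by a point or two.

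A second skewed model, with a constant shift of 3.5 points and an SD of change close to 7.82, gives a milder picture at low r:

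| r (assumed) | Rank-sum | Signed-rank |
|---|---|---|
| 0.3 | 92% | 90% |
| 0.5 | 85% | 90% |
| 0.7 | 63% | 90% |
| 0.9 | 5% | 91% |

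With normal data and the same 3.5-point shift, rank-sum power is 66%, 51% and 25% at r = 0.3, 0.5 and 0.7, against 78–79% for signed-rank. Under the plan's rule, though, normal data would normally go to the paired t-test, so these figures should not be taken as the size of the problem.

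**The case against.** The strongest reply is that this is a slip in a name. The term stands beside the paired t-test, is attached to changes within each group, and is followed in the same sentence by "Mann–Whitney U test for differences between the two groups". Two names in one sentence suggest that two tests were meant, and a competent analyst would probably run the signed-rank test. That reading is likely right, so it cannot be said that the data will in fact be analysed without pairing. But intent does not correct the text. The wording occurs twice, and nothing elsewhere in the article resolves it.

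Three stronger readings are tempting and are not supported.

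- **A reader might infer that the primary comparison is compromised.** It is not. The study objectives and endpoints define superiority as a between-arm contrast, the sample size is for that contrast, and the tests named for it are appropriate to independent groups. The power figures above concern change within one arm only.
- **A reader might infer that real regression will be missed, or false regression claimed.** With positive r the error is conservative, so it does not create false claims of within-arm change. Whether it hides real change depends on r, the skew and the size of the change, none of which the article gives. The article also does not say whether 7.82 is the SD of the change or of a single measurement.
- **A reader might infer that one arm could be tested by the t-test and the other by the rank test, so that they differ only because of the method.** The Statistical analyses section does not say that the test is chosen separately by arm.

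**Conclusion.** The point holds as an error in the stated method, with limited reach. The article twice names an independent-samples test for paired data and never names the correct one. If the text is followed, non-parametric within-arm p-values are too large whenever r is positive, which is to be expected for repeat scans of one segment. Type I error is then about 2%, 0.5% and 0.1% or less at r = 0.3, 0.5 and 0.7.

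The power loss is conditional. It is little or none at low r in one skewed model, and from 83% down to 15% at r = 0.8 in the other. The range rests on assumed correlations, skew and effect sizes, with 42 pairs taken from the plan's evaluable number per arm. The between-arm superiority analysis and the sample size of 53 per arm stand unchanged.

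**What to change.** In the Statistical analyses section, replace rank-sum with signed-rank in both sentences on changes within each group: the one on percentage and absolute NCV, and the one on the secondary VH-IVUS, grey-scale IVUS and angiographic parameters. Keep the Mann–Whitney U test for between-group differences.

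The cost is two wording changes. Patients, procedures, data collection and sample size are not touched. With the signed-rank test, within-arm type I error returns to about its nominal level (4.2% to 5.9% in simulation at every correlation tried).

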**Figure Fig1:**
[figure not shown]
**Fig. 1** A Brief Flowchart of the Study

In non-diabetic patients with suspected CAD, coronary angiography (CAG) will be performed with the standard technique. Percutaneous coronary intervention (PCI) will be performed in culprit lesions based on the decision of an interventionist in participating centers within Korea [14]. Non-culprit lesions (index lesions) with intermediate stenosis (percentage diameter stenosis, 30–60%) by CAG will be evaluated by VH-IVUS if the patients meet the study inclusion and exclusion criteria. Data will be stored for off-line analysis.

Patients will be randomized at ratio of 1:1 using a random table (made by matches of age, sex, presentation of coronary artery disease and sequentially numbered) to receive either rosuvastatin 10 mg plus fenofibrate 160 mg or rosuvastatin 10 mg alone. Study drugs will be administered after the index VH-IVUS. Biochemical laboratory tests (fasting state) will be performed at the time of CAG and followed up at the third month (±2 months) and 12th month (±2 months). Follow-up CAG and VH-IVUS examination will be performed at the 12th month (±2 months). Clinical events will be followed up by office visit or by telephone contact if necessary. Adherence to the study drugs will be checked at every outpatient visit, and the decision to discontinue any of the study drugs will be discussed and checked under the recommendation of the responsible cardiologist. Other drugs which influence lipid profiles will be prohibited during the trial period.

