### Study population and entry criteria

Inclusion criteria are as follows: (1) age ≥ 20 years; (2) presence of non-culprit intermediate lesions confirmed by index CAG; and (3) combined dyslipidemia (baseline LDLc ≥ 70 mg/dL and non-HDLc ≥ 130 mg/dL in statin-naïve patients, and baseline LDLc ≤ 100 mg/dL and non-HDLc ≥ 100 mg/dL in patients on statin treatment). A non-culprit lesion is defined as a VH-IVUS-feasible native coronary lesion with 30–60% stenosis, 2.0–4.0 mm in diameter by visual estimation during CAG, and located more than 10 mm apart from the intervened lesion.

Exclusion criteria are as follows: (1) diabetic patients; (2) poor cardiac, renal, or hepatic function; (3) explicit side effects and/or contraindications to lipid-lowering agents, including pregnancy, breastfeeding, and familial hypercholesterolemia; (4) very high triglyceridemia (TG ≥ 500 mg/dL); (5) lesions that might cause difficulties for VH-IVUS. Detailed inclusion and exclusion criteria are summarized in Table 1.

**Table 1 Tab1:** Inclusion and exclusion criteria

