**Fig. 2 Fig2:**
[figure not shown]
Schedule of enrolment, interventions, and assessments

Written informed consent for subjects who meet clinical and angiographic inclusion and exclusion criteria will be obtained by an investigator. Personal information is planned to be corrected by interview and chart review. All personal information will be protected by an encoding process. Potential participants are informed of the purpose of the study, the potential hazards and risks, the potential benefits, the procedure, and the expected follow-up after intervention. They are informed that participation is voluntary and that withdrawal from the study may occur at any time. On the consent form, participants will be asked if they agree to the use of their data should they choose to withdraw from the trial. Participants will also be asked for permission for the research team to share relevant data with people from the universities taking part in the research or from regulatory authorities, where relevant. This trial involves collecting biological specimens for storage. Additional permission for storage and measurement of biological specimens will be acquired from participants according to the local IRB’s requests.

After the subjects are enrolled in the present study, subjects will be randomized to two groups using a random box table made by stratified randomization according to subjects’ age, sex, and clinical presentation (acute coronary syndrome or not).

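### The primary comparison is an unadjusted test of change in percentage NCV: valid, but it leaves out the randomisation strata and prior statin use, fixes the baseline slope at 1, and so gives up precision

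*Protocol article*

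**What the plan says.** - **Primary test.** The Study endpoints section makes the primary endpoint the between-group comparison of the 12-month change in percentage and absolute NCV. The Statistical analyses section tests it by an unpaired t-test or "Mann–Whitney U test for differences between the two groups". Continuous variables are to be compared by one or the other according to normality. No covariate is named.
- **Randomisation.** Under Randomization, interventions, and data assessment, patients are allocated "using a random box table made by stratified randomization according to" age, sex and clinical presentation (acute coronary syndrome or not). Study design and subjects describes a table "made by matches of age, sex, presentation of coronary artery disease and sequentially numbered".
- **Prior statin use.** Study population and entry criteria sets one pair of lipid limits for statin-naïve patients and another "in patients on statin treatment". Prior statin use is neither a randomisation factor nor a term in the primary test.
- **Regression.** A multivariable linear regression is planned to find independent predictors of the fall in percentage NCV. Its covariates are not listed, and it is not presented as the treatment comparison.
- **Sample size.** The aim of the calculation is given as "to detect a difference of 4.78 in percentage NCV", and the error rate is set by testing "with a two-sided alpha level of 0.05". On size, the section reports that "a sample size of approximately 42 patients per treatment group was calculated to provide 80% power". The spread enters by "assuming a standard deviation of 7.82", and the section does not say whether this SD is that of the change or of a single measurement.

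**The concern.** The analysis does not use what the design provides, in four respects.

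1. **Baseline.** A change score subtracts baseline with a slope fixed at 1. When the correlation rho between baseline and follow-up is below 1, that over-corrects. The arm that happens to start with more necrotic core will tend to show the larger fall.
2. **Strata.** Balancing the arms on prognostic factors and then omitting them leaves their variance in the standard error, although the design has removed it from the treatment contrast. The test becomes conservative.
3. **Prior statin use.** Statin-naïve patients start a statin at randomisation; the others already take one. The two groups could plausibly change differently, and only chance balances them across the arms.
4. **Choice of test.** Moving between a t-test and a rank test on observed normality makes the quantity estimated depend on the data: a mean difference in one case, a rank ordering in the other.

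With about 42 evaluable patients per arm, and a study population that the article itself calls relatively small, precision from variables already collected is worth having.

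**Working it through.** **Inputs from Sample size calculations:** difference 4.78, SD 7.82, two-sided alpha 0.05, power 80%, 42 per group, dropout 20%. **Assumptions, because the article gives no figure:** rho, shown from 0.3 to 0.9, and the share R² of outcome variance explained by the strata, shown at 5%, 10% and 20%.

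**1. The plan's own figure.** n per group = 2(1.960 + 0.842)² × 7.82² / 4.78² = 42.0. Strict rounding up gives 43, which agrees with a stated figure of approximately 42. Power at 42 per group is 80.0% by the normal approximation and 79.1% by the noncentral t. Dropout: 42 / 0.80 = 52.5, so 53 per group. The sample size reproduces for exactly the unadjusted test that the plan names.

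**2. Baseline ANCOVA, reading 7.82 as the SD of change.** With equal variances s² at the two times, Var(change) = 2s²(1 − rho) and Var(ANCOVA residual) = s²(1 − rho²). Their ratio is (1 + rho)/2, so the ANCOVA SD is 7.82 × √((1 + rho)/2). Power is noncentral t at 42 per group; the last column uses the normal approximation.

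| rho | residual SD | power | n per group for 80% |
|---|---|---|---|
| change score | 7.82 | 79% | 43 |
| 0.3 | 6.30 | 93% | 28 |
| 0.5 | 6.77 | 89% | 32 |
| 0.7 | 7.21 | 85% | 36 |
| 0.9 | 7.62 | 81% | 40 |

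**3. The other reading: 7.82 as a single-time SD.** The change SD is then 7.82 × √(2(1 − rho)) and the ANCOVA SD is 7.82 × √(1 − rho²). Power for change score against ANCOVA is about 65% against 83% (rho 0.3), 79% against 89% (rho 0.5) and 95% against 97% (rho 0.7). The direction is the same.

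**4. Omitted strata.** If the strata explain R² of the variance and are balanced among evaluable patients, the contrast has variance proportional to 1 − R² while the test assumes 1. True alpha = 2(1 − Φ(1.960/√(1 − R²))):
- R² = 5%: 1.960/√0.95 = 2.011, alpha 4.4%
- R² = 10%: 1.960/√0.90 = 2.066, alpha 3.9%
- R² = 20%: 1.960/√0.80 = 2.191, alpha 2.8%

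**5. Chance baseline imbalance.** One standard error of the baseline difference is √(2/42) = 0.218 SD. It moves the change-score contrast by (1 − rho) × s × 0.218. With the SD of change held at 7.82, s = 7.82/√(2(1 − rho)). The shift is 1.01 points (rho 0.3), 0.85 (0.5), 0.66 (0.7) or 0.38 (0.9), that is, 21%, 18%, 14% or 8% of the 4.78 target. It can go either way and averages zero over randomisations.

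**The case against.** The strongest reply is that nothing here is an error. An unadjusted test after randomisation is valid, and the plan was sized for that test and delivers the power it claims. Most of this stands, and it rules out several stronger readings that a reader might infer:

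- **That the test ignores baseline NCV.** It does not. The endpoint is a change, so baseline is subtracted for every patient. The fault is a fixed slope.
- **That the treatment effect is biased or type I error inflated.** The contrast is unbiased on average, and omitting prognostic strata makes the test conservative. Since both arms receive rosuvastatin 10 mg, prior statin use differs between arms only by chance.
- **That the sample size is wrong.** It reproduces. Lost power here means power above the planned level that is not taken up.
- **That the gain is known to be large.** It depends on undocumented quantities. At rho 0.9 it is about two percentage points (79% to 81%). The lower alphas need the strata to explain 10–20% of the variance and to stay balanced after dropout, and the article supports neither condition. It also gives no figure for how differently statin-naïve and statin-treated patients change.

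A further reply is that the planned multivariable regression may already contain treatment, baseline and prior statin use, and that covariate lists belong in the full protocol or analysis plan. The omitted list is indeed no finding. But the article states the purpose of that regression, which is a search for predictors, and names a different method for the treatment comparison. The regression therefore does not stand in for an adjusted primary analysis.

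**Conclusion.** The point holds as an avoidable loss of precision in a choice that the article fixes explicitly. The direction is secure: under equal variances, baseline ANCOVA has a smaller residual variance than the change score for any rho below 1.

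The size is not secure. Over rho 0.3 to 0.9, power at 42 per arm would be about 93% to 81% against 79% now, if 7.82 is the SD of change. True alpha would be about 4.4% to 2.8% if the strata explain 5% to 20% of the variance. Both ranges rest on assumptions that the article cannot confirm. The consequences are a wider interval than necessary, a somewhat conservative test if the strata are prognostic, and an estimate more exposed to chance imbalance, most plainly in prior statin use, which the design does not balance. The change is worth making but is not a condition for the trial's validity.

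**What to change.** Before database lock, pre-specify as the primary analysis a linear model (ANCOVA) of 12-month percentage NCV on treatment, baseline percentage NCV, age, sex, acute coronary syndrome (yes/no) and prior statin use (yes/no). Report the adjusted mean difference with its 95% confidence interval and heteroscedasticity-robust standard errors. This also fixes one estimand regardless of a normality check. Keep the unpaired t-test and the Mann–Whitney U test as sensitivity analyses, and use the same model form for absolute NCV and the other continuous IVUS endpoints. State that the predictor regression is separate and exploratory.

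**Cost.** No new data are needed: the covariates are randomisation factors, entry criteria or baseline measurements. With 84 evaluable patients and age as a single term, residual degrees of freedom fall from 82 (84 − 2) to 77 (84 − 7). The sample size need not change. Because the protocol itself names the test, the change is a protocol and analysis plan amendment. Under the Executive Committee section it would need that committee's approval, communication with the local IRBs and notice to the DSMB. The trial is open-label and reported 102 of 106 patients recruited, so the amendment should be dated and made before any comparison of outcomes by arm.
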